### 6.7.2 TIMING OF HIV INFECTION

An Endpoint Committee will review the results from the local laboratory and may request additional testing of stored blood in order to determine the timing of the first HIV positive result which will be categorised and managed as follows:

- |                                   |                            |
|-----------------------------------|----------------------------|
| ▶ HIV positive at enrolment visit | excluded from all analyses |
| ▶ HIV positive at visits 4-9      | PrEP analysis              |
| ▶ HIV positive at visits 10 on    | vaccine analysis           |

Although participants who test positive for HIV will have been infected at a date prior to the test, for the purpose of the analysis the timing of infection is taken to be the time of the first HIV positive sample.

See [section 6.14](#) for post-trial testing of participants who develop vaccine induced seropositivity (VISP).

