### 6.1 TRIAL ASSESSMENT SCHEDULE

The trial assessment schedule consists of a screening visit (visit 1), an enrolment visit which must take place within 8 weeks of the screening visit and which defines week 0 (visit 2).

The first injection will take place at week 0 (visit 2) and further injection visits are at visits 4, 8 and 12. The latest timepoint that the second, third and fourth injection visit can take place is indicated in Table 1 and is the end of the 13th, 40th and 68th week from enrolment respectively. Visits 3, 5, 6, 9, 10 and 13 have specific activities and procedures that relate to the collection of key safety and efficacy variables following the injection visits and the ideal timing relates to each injection. The earliest timepoint and upper target for visits is also given in Table 1. Provided visits occur in the period between the earliest timepoint and upper target there is no need to complete a protocol deviation form. If the participant has passed the upper target for the visit, a protocol deviation form should be completed.

Safety follow-up visits (or calls) to ask about all adverse events are at visits 3,5-7,9-11,13-15. After visit 15, follow-up visits will continue every 12 weeks for HIV testing through to the end of the trial, and participants will be asked about any serious illness or admission to hospital at these visits. These visits will continue to the last 3 months of the trial when everyone will have a final study visit. Additional visits may be undertaken if indicated, for example to investigate or follow-up an adverse event or abnormal laboratory result.

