### 6.3.1 ELIGIBILITY

Study staff will check that participants understand the key messages contained in the information sheet and listed in [section 6.2.1](#).

Study staff will review the routine laboratory parameters and screen for STIs collected at screening and determine whether there are any clinically relevant abnormalities that require further investigation prior to randomisation. STIs will be treated appropriately, but the participant can proceed to randomisation on the day, if otherwise eligible.

Participants will review any new adverse events or new medications since the screening visit and for female participants, any changes in contraception. All this information will be recorded on the appropriate CRF according to the SOM. The Risk assessment CRF will also be administered.

Study staff will review the risk of the participant acquiring HIV again to see if anything has changed since screening, and conduct a point of care HIV test in accordance with the LAP.

For female participants of childbearing potential a pregnancy test will be performed by analysis of a urine sample for Human Chorionic Gonadotrophin (HCG) and a negative result will be confirmed before each injection.

The review of Eligibility will be completed using the appropriate CRF.

Prior to randomisation, blood will be collected for 4th generation ELISAs, and to store for future immunological assays, HIV RNA, and intracellular tenofovir diphosphate levels.

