## 6.7 PROCEDURES FOR ASSESSING EFFICACY

For the vaccine analysis, the efficacy endpoint is HIV infection acquired after visit 9 by a participant who has received 3 vaccinations and is HIV negative at that visit. For the PrEP analysis, the efficacy endpoint is HIV infection acquired up to and including visit 9 by a participant who was HIV negative at week 0 (visit 2).

There are two aspects to consider: firstly the need to distinguish between HIV infection and a vaccine induced response, and secondly the need to determine the timing for the analysis.

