### 6.7.1 CONFIRMATION OF HIV INFECTION

HIV-uninfected individuals who participate in prophylactic HIV vaccine studies may develop HIV-specific antibodies because of an immune response to the candidate HIV vaccine, referred to as vaccine induced seropositivity (VISP). These antibodies may be detected in common HIV assays, causing the test to appear positive even in the absence of actual HIV infection.

Point of care tests will not be used during follow-up in order to ensure that staff remain blind to the allocation as responses to the recombinant protein vaccine may elicit reactions in the point of care tests.

Study staff will collect a sample in the appropriate tube for HIV ELISA assays and plasma for RNA viral load in case this is required. They will send the samples to the local laboratory at visits 2, 4, 6-15. Follow-up after visit 15 will continue for all participants with collection of a sample for HIV ELISA and RNA viral load every 12 weeks up to and including the final visit which will take place in the last 3 months of the study (2023-2024). The samples will be processed according to the LAP and HIV testing algorithm and any residual stored for future tests including assessment of resistance mutations. Samples collected at visits 2, 8 and 12 will not be processed in real-time as the next timepoint is within 2-4 weeks.

After determining HIV status in the local laboratory, the result will be returned to the clinic as:

- ▶ No evidence of HIV infection
- ▶ HIV infected

Samples will continue to be collected until it is possible to determine negative or positive status. Trial treatments can continue during this time.

Participants who are HIV positive will be counselled and given a letter of referral to their preferred provider of care and assisted with transport if necessary.

At the visit at which HIV status is confirmed as positive and the referral organised, 61ml of additional blood will be collected for humoral and cellular responses (see [sections 6.8.1](#) and [6.8.2](#)), virological analysis including resistance testing and drug levels if appropriate to the period of follow-up.

The 61ml of additional blood will be collected and stored for:

- 5ml CD4 T-cell count,
- 5ml plasma HIV RNA
- 4ml PrEP drug level testing
- 37ml cellular and humoral immune responses
- 10ml viral isolation and sequencing.

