### **9.2.2.B Secondary**

- ▶ An adverse event leading to a clinical decision to discontinue or interrupt the product schedule, regardless of relationship
- ▶ Serious adverse events (SAEs)
- ▶ Genotypic resistance at HIV seroconversion, focussing on the mutations selected by tenofovir and emtricitabine (codons 65, 70, 184 in reverse transcriptase).
- ▶ Adherence assessed by (a) self-report (b) results of point of care urine tests (c) TFFV-DP levels measured on DBS in red blood cells (d) total number of pills dispensed

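### Section 6.7.2 excludes participants HIV positive at enrolment from every analysis, whereas section 9.5 excludes them only from the primary efficacy analyses; the wording should be limited to efficacy

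*Protocol*

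**What the plan says.** Section 6.7.2 sorts participants by the date of the first HIV positive sample, as settled by an Endpoint Committee that may have stored blood re-tested. Those positive at the enrolment visit are "excluded from all analyses". Those first positive at visits 4 to 9 go to the PrEP analysis, and those first positive from visit 10 on go to the vaccine analysis.

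Section 9.5 is narrower. Section 9.5.1 removes participants who were positive by two weeks after the third immunisation from the primary vaccine efficacy analysis. Section 9.5.2 defines the primary PrEP analysis as modified intention-to-treat without those positive at enrolment. Neither extends the exclusion to safety or resistance.

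Resistance is a secondary outcome of the PrEP trial in section 9.2.2.B: "Genotypic resistance at HIV seroconversion, focussing on the mutations selected by tenofovir and emtricitabine". The trial summary lists it among the PrEP secondary safety outcomes, and the summary's heading for the primary safety outcome refers to both the vaccine and the PrEP analyses.

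On detection, section 6.3.1 has staff "conduct a point of care HIV test in accordance with the LAP" on the day of enrolment. Section 6.7.1 adds: "Samples collected at visits 2, 8 and 12 will not be processed in real-time as the next timepoint is within 2-4 weeks". While status is unresolved, "Trial treatments can continue during this time".

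**The concern.** Removing people who were already infected at enrolment is right for efficacy, because they cannot have a new infection. It is wrong for safety, where everyone who received product should count. It also loses information on resistance: someone who takes two-drug PrEP while already infected is a person in whom tenofovir or emtricitabine mutations are of direct interest, and TAF/FTC and TDF/FTC are being compared.

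The protocol uses the word analyses in a sense that includes safety and resistance. An analyst who follows 6.7.2 to the letter would therefore drop these participants from both, while one who follows 9.5 would not. Two instructions in one protocol lead to different analysis populations.

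**Working it through.** **Can people in this category have been exposed?**

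- The HIV check on the day of enrolment is a point of care test (6.3.1). A laboratory test was done at screening, up to 8 weeks earlier (6.1, 6.2.3).
- The visit 2 laboratory sample waits (6.7.1), and Table 1 schedules no HIV sample at visit 3. The next scheduled sample is at visit 4.
- The first injections are given at visit 2 (6.1), and 60 PrEP tablets are handed out then (6.3.4).
- Blood is stored at enrolment for HIV RNA (6.3.1), so an infection can later be dated back to enrolment.

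So yes. A person dated back in this way may also seroconvert while taking study PrEP, which fits the resistance outcome as worded.

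**Do other passages restore them?** Section 5.7 asks anyone with one injection or one tablet to stay in follow-up, and includes data already collected from people who stop early. Section 6.7.1 continues follow-up after an HIV diagnosis, partly for safety, and takes blood for resistance testing when infection is confirmed. These passages show that the data are collected. None states that enrolment-positive participants enter the safety or resistance analyses.

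**How many people?** The protocol gives no expected number, so there is no figure to reproduce. Two rough routes, with N = 1668:

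- Proportion in the earlier vaccine trial described in section 1.2: 7/16402 = 0.043%, so 1668 × 7/16402 = 0.7.
- Incidence of 4/100 person-years (section 9.3.1) with an assumed undetected window of w weeks: 1668 × 0.04 × w/52. This gives 2.6 for w = 2 and 5.1 for w = 4. The window is an assumption; the protocol states none.

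These counts are upper limits for PrEP exposure, since section 5.7 does not oblige participants to start PrEP.

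**Against what?** Person-years to visit 9, taken as half a year with 10% loss: 1668 × 0.5 × 0.9 = 750.6. Expected infections = 750.6 × 0.04 × (1 − PrEP effectiveness):

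- 50% effectiveness: 15.0
- 70% effectiveness: 9.0
- 80% effectiveness: 6.0

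**Share of all infections up to visit 9, including those present at enrolment:**

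- Lowest: 0.7/(0.7 + 15.0) = about 4%
- Middle, at 70% effectiveness: 0.7/9.7 = about 7%; 2.6/11.6 = 22%; 5.1/14.1 = 36%
- Highest: 5.1/(5.1 + 6.0) = 46%

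**Share of the safety population:** at most 5.1/1668 = 0.3%.

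**The case against.** The strongest reply is that the entry classifies endpoints and does not define data sets. It stands under section 6.7, which has just set out what counts for efficacy: "For the PrEP analysis, the efficacy endpoint is HIV infection acquired up to and including visit 9", with a matching definition for the vaccine. If analysis in 6.7.2 also meant safety, the other two rows would make no sense: a participant first positive at visit 6 would count only towards PrEP safety, although that person had also been injected. On this reading the first row means only that the infection counts in neither efficacy comparison. This is a plausible account of the intention, and section 9.5 supports it. It does not settle the matter, because the row says all and no sentence narrows it.

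Two stronger inferences are tempting, and the protocol supports neither.

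- A reader might conclude that the sponsor has chosen to delete exposed participants from safety and resistance. Section 9.5, continued follow-up and resistance sampling at confirmation all point the other way, and serious adverse events are notified from randomisation regardless (7.3.1.E). What is established is a conflict in wording.
- A reader might conclude that a large share of PrEP-exposed infections, such as 22% to 36%, will be lost and resistance therefore understated. That share needs both the assumed window and 70% effectiveness. The only observed proportion in the protocol gives about 7% at the same effectiveness, though in a population whose incidence may have differed. Saying that resistance is understated would also need resistance rates in the two groups, which are not given.

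A separate SAP may define a safety population. If it includes everyone exposed, it would contradict 6.7.2 as it stands.

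**Conclusion.** The point holds as a conflict between 6.7.2 and the rest of the protocol, with a bad result if 6.7.2 is applied literally. For adverse-event rates the effect is negligible. For resistance it is uncertain: about 0.7 to 5.1 people, set against about 6 to 15 infections up to visit 9. The range rests on the earlier trial's proportion at one end and on an assumed 4-week window at the other, both with 1668 participants, and on a background incidence of 4/100 person-years with PrEP effectiveness of 50% to 80% for the comparison. With so few infections, even one or two cases are worth reporting. The efficacy exclusion itself is sound and should stay.

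**What to change.** Reword the first row of 6.7.2 to say that these participants are left out of the efficacy analyses, in line with 9.5.1 and 9.5.2. Add that anyone who received an injection or a PrEP tablet stays in the safety analyses. Add also that resistance in participants infected at enrolment and exposed to study PrEP is reported as its own group by PrEP agent. It should not be pooled with infections acquired after enrolment, because the two groups answer different questions.

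The cost is one line in the protocol and a matching line in the SAP. The visits, adverse-event records and samples are already planned.

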## 6.8 PROCEDURES FOR ASSESSING IMMUNE RESPONSES

Samples will be collected at visits 2, 6, 9, 13 and 15, and if they contract HIV at the visit a participant is informed that they have HIV infection. Further details on the timing of these samples and the window within which they are to be collected can be found in the SOM and LAP. Specimens will be collected, transferred to the local research laboratory, aliquoted and stored according to LAP. The aliquots will be used for the secondary and exploratory humoral responses.

Samples may be used for other testing and research related to furthering the understanding of HIV and the immune system. In addition, cryopreserved samples may be used to perform additional assays to support standardization and validation of existing or newly developed methods.

### 6.8.1 SECONDARY IMMUNE RESPONSES

The secondary immunological outcome is the quantitative binding antibody responses against CN54gp140 and AIDSVAX gp120 measured by ELISA.

Quantitative binding antibody ELISA assays will be performed in a single laboratory for the purpose of the trial analyses to minimise the risk of variability, but these assays can also be conducted locally as part of the capacity building where funding permits.

### 6.8.2 EXPLORATORY IMMUNE RESPONSES

The following exploratory immunological assays may be performed based on the initial results of the trial and the amount of funding available. These exploratory assays will provide an in-depth profiling of the quality of the immune responses, and enable the evaluation of immunological correlates of risks associated with HIV acquisition and ultimately identification of immune correlates predictive of vaccine efficacy.

- ▶ **Neutralizing antibody (nAb) responses:** HIV-1-specific nAb assays may be performed on serum samples from study participants. Tier 1 assays will test neutralization of HIV-1 strains represented in the highly neutralization sensitive tier 1 viruses. The tier 2 assays will test neutralization of a panel of heterologous primary isolates.
- ▶ **Binding antibody responses** measured by binding antibody multiplex assay (BAMA): Total binding IgG antibodies to HIV-1 Env proteins (including V1/V2 regions of interest) will be

measured on serum samples from study participants. Specimens from other HIV antigens and Ab isotypes may also be assayed based on the results of the initial assay.

- ▶ **ADCC and other functional antibody responses:** antibody-dependent cell-mediated cytotoxic activity and other antibody functional assays may be performed
- ▶ **Frequency of CD4 and CD8 T cell producing cytokines** will be assessed as an exploratory immunological outcome by multiparametric flow cytometry after in vitro stimulation of thawed PBMC with HIV-specific antigens using intracellular cytokine staining (ICS) including, but not limited to IFN $\gamma$ , IL-2, and TNF $\alpha$ . Additional assays may be performed to further investigate the immune responses elicited by the study vaccine regimens. Examples include, but are not limited to additional binding antibody assays, and supplemental cellular assays (T cells and B cells).

A single laboratory will conduct each of the assays for the purpose of the trial analyses, but assays can also be conducted locally as part of the capacity building where funding permits.

### 6.8.3 GENOTYPING

Molecular human leukocyte antigen (HLA) typing may be performed on enrolled participants using cryopreserved PBMC collected at baseline, initially on specimens from participants who demonstrate vaccine-induced immune responses following vaccination. Other participants (including placebo recipients) may be HLA-typed to support future immunological studies. The genetic testing will be limited to genes related to HIV and the immune system.

## 6.9 PROCEDURES FOR ASSESSING CONTEXTUAL DATA

### 6.9.1 SELF-REPORTED SEXUAL AND ADHERENCE BEHAVIOURS

Self-reported sexual and adherence behaviours will be collected in the CRF and supported by the PrEP diary card.

The **PrEP diary card** will be a simple record for noting pill taking and acts of sexual intercourse when a condom was used or not, in order to determine pill use in the 2 days before and following sex acts without a condom. The facility to enter this information directly into an application on a smartphone may be available for participants that have secure access to a mobile phone with capacity to host the application. Participants will be invited to share their record with staff during a study visit to assist in accurate completion of the CRF. Self-report will be checked against the result of the point of care urine test. Study staff will be prompted to ask an open question about discrepancies between reported pill use and objective measures of drug. The answers will be recorded on the CRF and may be entered into software designed to analyse free text.

Participants will be asked about pill taking in the 2 days prior to the visit, and the 2 days before and after the last sex act without a condom when they attend the study visits to collect drug,

**Questions** to capture risk behaviours will be completed at screening, visits 2, 4, 6, 7, 8-10, 12, 14, and 15 and every 24 weeks thereafter until the end of the study.

**In depth interviews** (one to one discussions) will be conducted in up to 10% of participants purposively selected to represent the patterns of risk and adherence behaviours emerging from the quantitative data and these interviews will provide insights into the motivations and barriers that facilitate and obstruct behavior change respectively. The one to one discussions will be explained to the participants using the Supplementary Participant Information Sheet and written informed consent will be collected prior to participation by an individual trained in interview techniques. The interviewer will be provided with a summary of the information collected on the CRF. They will interview participants about sexual and adherence behaviours, study and PrEP acceptability using the one to one discussion guide.

**Group discussions** may be conducted with a subset of participants (with approximately 8 participants per group) by staff trained in the technique who are independent of the clinic team. Some participants will be purposefully selected for participation in group discussions and others will be invited on an ad hoc basis. Selection will be directed after the social science group review of the summary quantitative data. The group discussion will be explained to participants using the Supplementary Participant Information Sheet and written consent collected on the Consent Form .

**Structured debriefs** of community and counselling staff will be conducted by a social scientist during the course of the study. Typically, these will note conversations observed or initiated by staff with and between participants, non-participants, clinic staff and community workers. The notes will be anonymous and recorded using a template.

#### **6.9.2 CONTEXTUAL DATA IN SEROCONVERTORS**

Participants who seroconvert at any time during follow-up will also be invited to take part in an in-depth interview as described above. Information about sex acts without condoms or PrEP since the previous negative result, the number and characteristics of new partners will be collected.

### **6.10 EARLY STOPPING OF FOLLOW-UP**

If a participant chooses to discontinue their trial treatment, they should continue to be followed up. If they do not wish to attend any further visits then their decision must be respected. The MRC/UVRI and LSHTM should be informed of this in writing according to the SOM.

If the participant is willing to complete interviews and provide samples at the time of their last visit then study staff should follow the schedule for visit 9 for participants who leave the study prior to this visit , or visit 15 for those leaving later.

The data already collected in the trial will have been extracted from the study database for monitoring and analysis purposes, and cannot easily be redacted. The data will not contain name and date of birth. The consent provided at screening will be assumed to apply for future use of these data in analyses for public health benefit.

Where possible study staff will check that the participant still consents to the future use of stored samples already collected, and if this is refused the samples will be located using the unique trial identifier and destroyed. If it is not possible to check consent, then the consent provided at screening will be assumed to apply. The samples will not contain any personal identifiers such as name and date of birth.

Participants may change their mind about stopping trial follow-up at any time and re-consent to participation in the trial, if this is practical in relation to the time they enrolled and the time since they decided to stop follow-up.

The IDMC and TSC may make a recommendation to amend follow-up following the interruption or discontinuation of product.

